### Allocation and blinding

After completing the baseline workup (Fig. 1), patients are allocated to consecutive randomization numbers. Randomization has been performed by the pharmacy at Odense University Hospital in blocks of four. The allocation code is blinded to both patients and investigators and is solely known by the pharmacy. Opaque envelopes containing the individual allocation are available on site in case of the need for emergency unblinding. If the allocation code is revealed before completing the trial the patient will be excluded.

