## Methods

One hundred seventy kidney transplant patients will be included from four Danish hospitals covering all Danish renal transplant centers (Odense, Copenhagen and Aarhus). Patients are recruited from outpatient clinics in the Departments of Nephrology at Odense University Hospital, Kolding Hospital, Rigshospitalet, Copenhagen and Aarhus University Hospital, respectively. Eligibility criteria are listed in Table 1.

**Table 1 Tab1:** Eligibility criteria

Inclusion criteria	Exclusion criteria
Age > 18 years	Former intolerance of spironolactone
Tacrolimus/cyclosporine treatment	Potassium binder or digoxin treatment
Proteinuria < 3 g/day	Pregnancy or planned pregnancy
Creatinine clearance ≥30 mL/min	Clinically relevant organic, systemic or psychological disorder
Plasma potassium < 5.5 mmol/L	Expectation of non-compliance
Negative pregnancy test at inclusion for women of childbearing potential and adequate contraception throughout the trial	

Wide eligibility criteria have been chosen to obtain a high generalizability of the results. This study includes renal transplant patients with a stable kidney function at the time of inclusion. Even in stable patients, a gradual deterioration of renal function is expected. Previous studies have found an average rate of decline of glomerular filtration rate in of 1–3 mL/min/year [23–26]. Hence, we chose a follow up of 3 years.

Patients are randomized 1:1 to spironolactone (Spirix®) or placebo for three years. Initial dosage is 25 mg once daily, which is doubled after three months, if tolerated well. At inclusion and yearly hereafter a standard workup is performed including chrome-EDTA clearance, 24-h urine collection, electrocardiogram, 24-h ambulatory blood pressure measurement and blood- and urine samples (Fig. 1). Anonymized samples are stored at − 80 °C until analyses. In a subgroup (*n* = 50) graft biopsies will be performed at inclusion and after two years. All registrered variables are listed in Table 2.

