### Withdrawal

Withdrawal criteria include a sustained compliance of less than 80%, hyperkalemia despite reduction of dosage or intolerable side effects.

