### Statistical methods

All statistical analyses will be done using STATA software. All generated variables will be documented by do-files. The main analysis will be performed as intention-to-treat using last-observation-carried-forward. Sub-analyses will include per protocol analyses and “best case”/“worst case” analyses. Where appropriate, variables will be analyzed using parametric or non-parametric tests.

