## Discussion

Long term kidney graft survival is a key issue in transplant medicine. Chronic CNI nephrotoxicity contributes to late allograft loss [3]. There is increasing evidence, that aldosterone plays a role in detrimental processes beyond fluid and sodium homeostasis e.g. inflammation and fibrosis, thereby possibly contributing to allograft failure [7]. Several animal studies have shown an effect of MR antagonism in reducing CNI nephrotoxicity [30]. The few available human studies addressing this hypothesis have been underpowered or focused on short term effects [19, 22]. This study aims to provide sufficiently powered evidence regarding the effect of long term MR antagonism on GFR and the development of kidney fibrosis in prevalent kidney transplant patients.

Concerns have been raised regarding MR antagonism in patients with impaired renal function due to the risk of hyperkalemia, which is a potentially lethal side-effect. In the wake of the Randomized Aldactone Evaluation Study (RALES) - a randomized, clinical trial investigating the effect of spironolactone in patients with congestive heart failure and serum creatinine below 221 μmol/L - there was a significant increase in hospitalizations due to hyperkalemia from 2.4 to 11.0 per 1000 patients [32]. The risk of hyperkalemia increases as GFR deteriorates. One safety study of MR antagonist eplerenone 25 mg/day for 8 weeks in 31 kidney transplant patients found a significant increase in plasma potassium during eplerenone treatment, however there was only one incidence of moderate hyperkalemia (> 5.5 mmol/L) and no patients were withdrawn from the study due to hyperkalemia. It was concluded, that MR antagonism is safe in kidney transplant patients with a GFR > 30 mL/min, but warrants close monitoring of plasma-potassium [33].

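### The rule that excludes any patient whose code is broken either contradicts the intention-to-treat analysis or cuts off that patient's follow-up, and must be reconciled with it

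*Protocol article*

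**What the plan says.** Four places in the Protocol article bear on this point.

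- **Allocation and blinding.** After the baseline workup, "patients are allocated to consecutive randomization numbers". On code breaks: "Opaque envelopes containing the individual allocation are available on site in case of the need for emergency unblinding". The section ends with the rule at issue: "If the allocation code is revealed before completing the trial the patient will be excluded". No condition is attached, and the sentence does not say what the patient is excluded from.
- **Statistical methods.** "The main analysis will be performed as intention-to-treat using last-observation-carried-forward". Unblinded patients are not named as an exception. The restricted population comes second: "Sub-analyses will include per protocol analyses and" best-case and worst-case analyses.
- **Withdrawal.** "Withdrawal criteria include a sustained compliance of less than 80%, hyperkalemia despite reduction of dosage or intolerable side effects". A broken code is not on this list.
- **Methods.** "Patients are randomized 1:1 to spironolactone (Spirix®) or placebo for three years", with chrome-EDTA clearance measured at inclusion and yearly after that.

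**The concern.** An intention-to-treat analysis keeps every randomised patient in the assigned arm whatever happens later. A rule that removes patients because of something that happens after randomisation works against this, and the comparison stays unbiased only if the removals are unrelated to outcome or fall alike in both arms.

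There is reason to doubt that here. The envelopes exist for emergencies, and patients who have one are plausibly in poorer condition than the rest. The arms may also differ in how often this happens. The Discussion raises concern about this drug class in impaired renal function "due to the risk of hyperkalemia, which is a potentially lethal side-effect", and says that plasma creatinine tends to rise when such drugs are started. This makes an imbalance plausible but does not establish one.

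At stake are the population of the primary analysis and the completeness of three-year clearance and cardiovascular follow-up. The rule also protects little for the primary endpoint: clearance is calculated from measured plasma radioactivity, and knowing the allocation gives little reason to discard such a value.

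**Working it through.** **1. The two readings of the rule.**

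| Meaning of exclusion | Under Statistical methods | Consequence |
|---|---|---|
| From the analysis | Contradicts intention to treat | Randomised patients leave the main comparison |
| From further participation | Compatible in form: the last value is carried forward | Later yearly clearance and later cardiovascular events are lost |

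The article does not choose between them. It speaks of withdrawal when a patient leaves the study (Safety, Withdrawal) and of exclusion only here. That leans slightly towards the first reading but does not settle it.

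**2. The plan's own sample size.** Inputs from Sample size: difference 5 mL/min, SD 10 mL/min, 80% power, significance level 0.05 (taken as two-sided).

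n per arm = 2 × (1.960 + 0.842)² × 10² / 5² = 62.8, rounded up to 63, so 126 in total. The stated figure is reproduced.

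**3. Power is not the problem.** With 15% dropout, 170 × 0.85 = 144.5 patients remain and power is 85.2%. If 10 more are lost to code breaks, 134.5 remain and power is 82.6%. The issue is bias, which extra patients do not cure.

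**4. Possible shift on the first reading.** If a fraction p of one arm is dropped, and its mean would have been D below that of the patients who remain, the arm's mean rises by p × D. The article gives neither p nor D, so these values are assumptions:

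- p = 3%, D = 5: 0.03 × 5 = 0.15 mL/min
- p = 5%, D = 10: 0.05 × 10 = 0.5 mL/min
- p = 10%, D = 15: 0.10 × 15 = 1.5 mL/min

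In patient counts, with 170/2 = 85 per arm, the shift is k × D / 85: 2 × 10 / 85 = 0.2; 4 × 20 / 85 = 0.9; 8 × 20 / 85 = 1.9 mL/min.

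All of these put every code break in one arm. With breaks in both, the shift in the difference is p₁D₁ − p₂D₂. For example, 5% against 3%, both at D = 10, gives 0.5 − 0.3 = 0.2 mL/min.

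For scale, the standard error implied by the sample size is 10 × √(2/63) = 1.78 mL/min, so 0.5 is 0.5/1.78 = 0.28 standard errors and 0.5/5 = 10% of the target.

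**5. Possible shift on the second reading.** The formula in step 4 does not apply, because the patient stays in the analysis. Methods cites an average decline of 1–3 mL/min per year. A patient whose code is broken before the one-year visit, with the baseline value carried forward, has three years of decline unseen: 3 × 1 to 3 × 3, or 3–9 mL/min. After the two-year visit, one year is unseen: 1–3 mL/min. If 5% of one arm only were affected before the one-year visit, that arm's mean would look better by 0.05 × 3 = 0.15 to 0.05 × 9 = 0.45 mL/min. This assumes that these patients decline at the average rate.

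**The case against.** The strongest reply is that the rule stands in the section on blinding, not in the section on analysis, and never mentions the analysis. It may mean only that participation ends. Carrying the last observation forward is a method for patients who leave early, so the two sections would then be compatible, and the full protocol may define the term. This stands in part: a flat contradiction is not proven. It does not rescue the rule, because the milder reading still ends follow-up and puts an early value in place of the three-year one.

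Other objections limit what may be inferred:

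- **Triggers.** A reader might infer that codes are broken because of severe hyperkalemia or an unexplained creatinine rise. The article links these events to the drug but not to opening an envelope. Safety and Withdrawal route them to dose reduction, withdrawal or interruption of study drug.
- **Seriousness.** A reader might infer that every excluded patient is a serious case. The rule covers any revealed code and has no seriousness criterion.
- **Deleted safety data.** Nothing says that recorded adverse events are removed. Safety has all events during participation recorded, and an event that prompts a code break comes before it. Only events after the exclusion would go uncollected.
- **Direction.** A bias in favour of spironolactone is possible but not shown. Whoever opens an envelope does so blind, and placebo patients have emergencies too.

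The best-case and worst-case sub-analyses are partial cover. The article does not define them, and they help only if code-broken patients remain in the population analysed.

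**Conclusion.** The point holds as one of inconsistency and a badly fixed rule. Followed as written, the sentence either removes randomised patients from an analysis described as intention to treat, or stops collecting their later clearance values and cardiovascular events. Both are worse than keeping them in, and nothing in the article reconciles the two sections.

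The size is unknown. The illustrations run from 0.15 to 1.9 mL/min in one arm's mean, about 0.5 at middle values, against a target of 5 mL/min. They rest wholly on assumed frequencies and deficits, and on code breaks in one arm only. The upper end needs both extremes at once, and breaks in both arms would partly offset. With few code breaks the effect would be small. The documents do not support the stronger conclusion that the worst treatment-related outcomes are deleted from the spironolactone arm.

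**What to change.** Reconcile Allocation and blinding with Statistical methods by replacing the sentence with:

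*If the code is revealed, the date and reason are recorded; the patient remains in scheduled follow-up and, as randomised, in the intention-to-treat and safety analyses; exclusion applies only to the per-protocol sub-analysis.*

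Whether study drug continues after a code break is a clinical matter outside this change. The amendment should be made before the trial is unblinded, and any patients already excluded under the rule should be listed by date and reason.

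The cost is one sentence and no visits beyond those already scheduled. The drawback is that a few patients are followed unblinded. That matters little for a laboratory-measured primary endpoint. It leaves somewhat more room for judgement in reported symptoms and events, which the recorded date of the code break makes visible.

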### Data management

All data will be documented for each visit in the respective Case Report Form and subsequently entered into the SPIREN project database. Data will be secured by double entry. The project database has been developed in cooperation with the Database Unit of the Region of Southern Denmark and complies with the standards of Good Clinical Practice.

### Statistical methods

All statistical analyses will be done using STATA software. All generated variables will be documented by do-files. The main analysis will be performed as intention-to-treat using last-observation-carried-forward. Sub-analyses will include per protocol analyses and “best case”/“worst case” analyses. Where appropriate, variables will be analyzed using parametric or non-parametric tests.

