### Outcome

Outcomes are summarized in Table 3.

**Table 3 Tab3:** Study outcomes

Primary endpoint	Secondary endpoints
Chrome-EDTA clearance	24 h urinary protein excretion
	Renal fibrosis (morphology)
	Cardiovascular events
	Biomarkers of fibrosis in tissue, blood and urine

The primary endpoint is renal function evaluated by chrome-EDTA clearance, in which glomerular filtration rate is calculated from the area under the plasma clearance curve after a single intravenous doses of ^51^CrEDTA. Plasma concentrations of ^51^CrEDTA can be determined with a single blood sample by measuring residual radioactivity 4 h after the injection or by multiple samples 4, 5 and 6 h after the injection. For centers using a single blood sample after 4 h, an additional blood sample is performed 24 h after the injection in male patients with plasma creatinine ≥200 μmol/L and female patients with plasma creatinine ≥150 μmol/L. In repeat chrome-EDTA clearance measurements the coefficient of variation is 8–10% [27].

Secondary endpoints include 24-h urinary protein excretion, cardiovascular events (death, myocardial infarction, stroke or peripheral arterial thrombosis) and renal fibrosis. For the latter, Masson Trichrome stained sections of kidney allograft biopsies will be used for measuring Banff chronicity scores and calculating morphologic fibrosis by point counting. Point counting provides a quantitative and reproducible estimation of the extent of fibrosis [28]. In brief, the software systematically selects sections of renal cortex and superimposes a grid on a computerized image. The extent of fibrosis is determined by counting the fraction of intersection points that overlie fibrotic areas relative to normal tissue. Limitations of both Banff scoring and point counting are the risk of sampling error as well as the somewhat subjective evaluation of fibrosis. In this study all biopsies will be reviewed by the same pathologist to avoid inter-observer variability.

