### Safety

Plasma potassium and -creatinine levels are monitored closely at initiation of therapy and after any dose adjustment. Sustained potassium levels > 5.8 mmol/L will result in reduction of dosage to 25 mg per day. In case of hyperkalemia on 25 mg per day, the patient will be withdrawn from the study. Potassium binding resins will only be used to handle cases of acute hyperkalemia, thus chronic treatment with resins is not allowed. Hyperkalemia is registered as an adverse event in case of an absolute increase of > 1.5 mmol/L or any increase to a level above 5.5 mmol/L. All significant increases in plasma creatinine are evaluated by study investigators, and in case of doubt of the etiology, the study drug is discontinued until renal function has stabilized. All adverse events registered throughout participation in the study will be recorded. Serious adverse events are defined according to Good Clinical Practice as events that result in death, are life threatening, require hospitalization, cause prolongation of existing hospitalization or result in persistent or significant disability/incapacity. The project safety board continuously monitors serious adverse events to identify general study safety issues.

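### Carrying the last chrome-EDTA clearance forward as the main analysis conflicts with the yearly GFR decline the trial expects, and can bias the treatment difference by an amount and in a direction that depend on who withdraws and when

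*Protocol article*

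**What the plan says.** The Outcome section of the protocol article defines the endpoint: "The primary endpoint is renal function evaluated by chrome-EDTA clearance". Under Statistical methods, the missing-data rule is fixed without a stated reason: "The main analysis will be performed as intention-to-treat using last-observation-carried-forward". The same section adds supporting analyses: "Sub-analyses will include per protocol analyses and" best-case and worst-case analyses.

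The Methods section describes the expected course of the endpoint: "Even in stable patients, a gradual deterioration of renal function is expected". It cites an "average rate of decline of glomerular filtration rate in of 1–3 mL/min/year" and draws the length of the trial from it: "Hence, we chose a follow up of 3 years". On timing it says: "At inclusion and yearly hereafter a standard workup is performed including chrome-EDTA clearance". Table 2 confirms years 0, 1, 2 and 3.

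The Safety section contains a route out of the study that is tied to a known drug effect: "In case of hyperkalemia on 25 mg per day, the patient will be withdrawn from the study". The Withdrawal section adds intolerable side effects and sustained low compliance. Sample size assumes an SD of 10 mL/min, a difference of 5 mL/min and 15% dropout, with no split by arm.

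**The concern.** LOCF treats a patient's clearance as unchanged from the last measurement to year 3. The trial's own rationale is that clearance does change, steadily and downwards, and that three years are needed to see it. The main analysis and the design premise therefore contradict each other.

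This would matter little if exits were few, late and unrelated to treatment. But the withdrawal rules include hyperkalemia and intolerable side effects, and the Discussion names hyperkalemia as a risk of the drug class. More exits on spironolactone are foreseeable. If those patients are held at early, higher values, part of the year-3 difference reflects who left and not how kidneys fared. At stake are the primary estimate and its p-value.

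**Working it through.** **Inputs from the document.** SD 10 mL/min, difference 5 mL/min, power 80%, significance level 0.05, dropout 15%, total 170 (Sample size); 1:1 allocation, hence 85 per arm; decline *s* = 1 to 3 mL/min/year; visits at years 0, 1, 2, 3 (Methods).

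**Assumptions of this check.** Two-sided test; the split of dropout by arm; the timing of exits; the same decline in both arms under the null; SD unchanged by LOCF.

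**The plan's own figure.** n per arm = 2 × (10 × (1.960 + 0.842) / 5)² = 62.8, so 63 per arm and 126 in total. This reproduces.

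**Decline omitted per patient** = *s* × (3 − year of last value):

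| Last value | Years missed | Omitted decline (mL/min) |
|---|---|---|
| Baseline | 3 | 3 to 9 |
| Year 1 | 2 | 2 to 6 |
| Year 2 | 1 | 1 to 3 |

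**Bias of the difference with no true effect** = (dropout on spironolactone − dropout on placebo) × *s* × years missed. The standard error is 10 × √(2/85) = 1.53 mL/min. The rejection rate is 1 − Φ(1.96 − bias/1.53) + Φ(−1.96 − bias/1.53). With 15% overall and every exit before year 1:

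| Split (spironolactone/placebo) | Bias for *s* = 1 to 3 (mL/min) | Type I error |
|---|---|---|
| 15%/15% | 0 | 5.0% |
| 18%/12% | 0.06 × 3 × *s* = 0.18 to 0.54 | 5.2 to 6.4% |
| 20%/10% | 0.10 × 3 × *s* = 0.3 to 0.9 | 5.4 to 9.0% |

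If the last value is year 1, the biases are two thirds of these; for 20%/10% that is 0.2 to 0.6 mL/min and 5.2 to 6.8%. If it is year 2, they are one third.

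**Balanced dropout with a true effect.** Let the 5 mL/min difference build up linearly and let 15% leave each arm. LOCF then estimates 5 × (0.85 + 0.15 × L/3), where L is the year of the last value: 4.25 (L = 0), 4.50 (L = 1) or 4.75 (L = 2). Power at 85 per arm is 79.1%, 83.5% or 87.2%, against 90.3% for an undiluted 5 mL/min.

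**Direction.** The Discussion describes an early creatinine rise on these drugs that reverses on stopping. Suppose measured GFR also dips by *h* = 2 to 5 mL/min on drug (an assumption; no size is given), that it recovers after stopping, and that an on-drug value at year 1 or 2 is carried forward. With a 20%/10% split and *g* years missed, bias = 0.20 × (*g* × *s* − *h*) − 0.10 × *g* × *s*. The extremes are 0.20 × (6 − 2) − 0.10 × 6 = +0.2 and 0.20 × (1 − 5) − 0.10 × 1 = −0.9 mL/min.

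**The case against.** The strongest reply is that the harm may be small. At the planned 15% dropout, a moderate imbalance moves the difference by a few tenths of a mL/min, against a target of 5. The document gives limited grounds for a large imbalance: the Safety section places dose reduction before withdrawal, entry requires potassium below 5.5 mmol/L, and the Discussion cites an eplerenone study in 31 transplant patients with no withdrawals for hyperkalemia (although at 25 mg/day for 8 weeks). Best-case and worst-case analyses are also planned. The point on size stands. The sub-analyses do not change which estimate and p-value are primary.

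A reader might infer more than the document supports, in four ways.

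- **Larger error inflation.** Losing 20% against 5% before year 1, then 5% a year in both arms, gives a bias of 0.43 × *s*, or 0.4 to 1.3 mL/min. By the same normal formula the type I error is 5.9 to 13.3%. But that scenario means 1 − 0.80 × 0.95² = 27.8% against 1 − 0.95³ = 14.3% dropout, about 21% overall, with the whole imbalance placed where LOCF is worst. The plan expects 15%.
- **Spironolactone necessarily favoured.** Under steady decline the arm with more early exits gains, but a reversible on-drug dip could cancel or reverse this.
- **All stoppers scored as not declining.** That is literally true only for exits before year 1; later leavers keep the decline seen up to their last visit.
- **Graft loss scored at the last value before failure.** The article does not say how graft loss is scored, so this is inference.

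It is also fair to say that a mixed model is not automatically unbiased. The Discussion notes that hyperkalemia risk rises as GFR falls. With only yearly clearance, withdrawal may depend on GFR values that were never measured.

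**Conclusion.** The point holds in a limited form. The main analysis assumes no change after the last visit, in a trial whose length is justified by expected change and whose withdrawal rules are plausibly related to treatment. Following the rule as written gives an estimate that is diluted when dropout is balanced and a real effect exists, and distorted when dropout is unbalanced. At 15% overall dropout, splits up to 20%/10% and all exits before year 1, the null bias is at most 0.9 mL/min (18% of the design difference) and the type I error at most about 9%. Both are smaller if exits come later, and there is no null bias if dropout is equal. These figures rest on an assumed split and on steady, common decline; neither sign nor size can be settled from the document. The conflict between LOCF and the expected decline is certain; the damage is probably modest unless the imbalance is large.

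**What to change.** Before unblinding, and by documented amendment because Trial status reports a between-group interim comparison in 2015:

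1. Make the main analysis a likelihood-based mixed model for repeated measures on all observed yearly chrome-EDTA values of every randomised patient, with treatment-by-visit terms and baseline included, and name the year-3 difference as the primary contrast.
2. Keep LOCF and the planned best-case and worst-case analyses as sensitivity analyses.
3. Add a delta-adjusted analysis that shifts the values expected for withdrawn patients over a stated range, since withdrawal may depend on unobserved GFR.

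This needs no new data and can be run in STATA. The cost is the amendment and a slightly larger standard error, because imputed values no longer count as observed. As a rough guide, if only the 72 per arm expected to complete (170 × 0.85 / 2) contributed, the standard error would be 10 × √(2/72) = 1.67 mL/min instead of 1.53, and power for 5 mL/min about 85%, still above the planned 80%. The earlier visits of withdrawn patients should recover part of that loss.
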